### Sample size

We used Arend and Shäfers’ (92) simulation-derived and case-sensitive guides to determine the sample size for adequate power in the primary analyses. We aim to recruit 65 participants so that for 7 observations per participant (data from sessions 5 to 12) in the primary analysis we could detect small-medium level one effects (standardized fixed-effect size = 0.18) with 0.8 power at a significance level of 0.05 and assuming a large intraclass coefficient of 0.5 (92). We plan to use full maximum likelihood estimation so that nested models that differ in fixed effects may be compared with likelihood ratio tests. The target sample size would be sufficient to provide accurate fixed effect estimates when using full maximum likelihood estimation, based on simulation-derived guidelines (95, 96).

If the actual sample size is low (less than 50), we will use restricted maximum likelihood estimation with small sample corrections so that estimation is unbiased (sample size as low as 15 can return accurate estimates with this method (96). In this case, for the primary analysis, we would focus on the core linear discrepancy model and conduct CRA. We would not be able to test whether complex or non-linear discrepancy models fit the data better than linear discrepancy effects because restricted maximum likelihood estimation doesn’t permit meaningful comparison of models that differ in fixed effects. Arend and Shäfers’(92) guidelines suggest that a medium level one effect could be detected with sample size as low as 30 people with 5 observations, 0.8 power at a 0.05 significance level, and large intraclass correlation (0.5).

Digital EMA is well accepted and feasible in psychiatric populations (97). However, missing data is expected and will be handled through maximum likelihood estimation, assuming it is missing at random (98).

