#### Exposure interventions

Exposure is a central feature of the planned intervention. Participants develop one or more hierarchies of feared/avoided social situations and are then supported to systematically approach these while dropping subtle avoidance and anxiety-driven coping strategies called *“safety behaviors.”* These exposures are framed as behavioral experiments with a threat prediction testing rationale rather than a habituation rationale. Exposures begin from session 5 and are set for homework until the end of treatment. In session 5, the participant and therapist develop one or more graded hierarchies of feared social situations (depending on the needs of the participant) to work through in treatment. Participants are encouraged to do exposures from their hierarchies for homework from session 5 onward.

All exposures are determined collaboratively by the therapist and participant within the constraint that it targets the participant’s social threat cognition and associated social situation. Exposures will thus differ for each participant since they are determined based on individual needs. Examples of possible exposures include initiating conversation, talking in group conversations, dating, being assertive, talking to authority figures, eating in public, public speaking, dancing in public, or talking on the phone. The number of exposures completed for homework will likely vary for each participant, depending for example on participant motivation and compliance. Since the study will operate in pandemic conditions, homework exposures will adhere to any social distancing or lockdown regulations at the time.

In-session exposures that are guided by the therapist occur in sessions 5, 6, 7, 8, and 9. The session 5 exposure aims to introduce doing exposure using smartphone EMA while providing an early positive experience. Therapists and participants can choose the specific social activity, but the manual recommends choosing one that can be practical to complete in-session, relevant to the participant, achievable for the participant, but also that elicits anxiety. Examples could include giving a short speech or having a short social interaction. This could be with the therapist, people in the clinic, or people in short walking distance from the clinic.

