In line with learning theory, we hypothesize that people whose exposures since the last session (*t* – 1) went better than expected will have lower social anxiety symptoms and social threat appraisals at the next session (*t*). Specifically, when holding mean O and other controls constant, higher mean P in the preceding inter-session interval (i.e., between *t* – 1 and *t*) will be associated with lower social anxiety symptoms and social threat appraisals at the next assessment (*t*), on average. Conversely, when holding mean O and other controls constant, lower mean P will be associated with higher social anxiety symptoms and higher social threat appraisals at the next assessment, on average.

Hypotheses will be supported if both the following conditions are met; (1) the fixed effect coefficient for mean O is significantly different from zero and positive in sign and (2) the fixed effect coefficient for mean P is significantly different from zero and negative in sign (52). To determine whether the joint effect of these component variables on the outcome variable is more complex than a linear discrepancy effect, we will run a model including second-order terms (mean P^2^, mean P × mean O, mean O^2^) as predictors (47, 50, 53). Hypotheses will be supported if the simpler model fits the data better than the more complex model. Models will be run in R using the nlme or lmer package. We will use the maximum likelihood estimation method and compare model fit using likelihood-ratio tests.

We will separate within- and between-person information for all time-varying predictors using person-mean centering (90). In this method, the person-mean centered predictors are added to level one and their respective person-means are added to level two. The fixed effect coefficients for the person-mean centered predictors are estimates of purely within-person effects, without being confounded with between-person effects.

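### The stated 0.8 power is for a level-one effect, but the primary hypothesis needs the P and O coefficients both significant; at 0.8 each, the rule has about 0.64 power if the estimates are independent

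*Protocol article*

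**What the plan says.** **Sample size.** The section sets out to find a sample size giving adequate power in the primary analyses. The target is "We aim to recruit 65 participants", so that "for 7 observations per participant (data from sessions 5 to 12") "we could detect small-medium level one effects (standardized fixed-effect size = 0.18) with 0.8 power at a significance level of 0.05", assuming an intraclass correlation of 0.5. The source is a published simulation-based guide. If fewer than 50 are recruited, the section says a medium level-one effect could be detected with as few as 30 people and 5 observations, again with 0.8 power.

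**Analysis.** The decision rule begins: "Hypotheses will be supported if both the following conditions are met". The conditions are a significant positive coefficient for mean O and a significant negative coefficient for mean P. Both are estimated in one model that also contains prior-session symptoms, fear activation and habituation. A further condition is that the linear model must fit better than the one with second-order terms.

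**Exposure interventions.** "In-session exposures that are guided by the therapist occur in sessions 5, 6, 7, 8, and 9". Homework exposures are set until the end of treatment, but "The number of exposures completed for homework will likely vary for each participant".

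**The concern.** Power belongs to a decision rule. The Sample size section gives the power to detect an effect of a given size in a level-one coefficient and mentions no joint criterion. The Analysis section declares success only when two coefficients are both significant with opposite signs. Unless the two tests always succeed or fail together, the joint event is less likely than either alone, so 0.8 for each cannot be 0.8 for the rule.

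The consequence lies in how a negative result would be read. If one coefficient misses significance, readers will set that against a claimed 80% chance of finding the effect, and may take it as stronger evidence against prediction-error theory than the design can give.

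**Working it through.** **Inputs from the Sample size section:** N = 65, m = 7, effect b = 0.18, alpha 0.05, power 0.8. The tests are taken as two-sided, from the wording of the Analysis section.

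**Assumed, because the document does not give them:** equal effects of 0.18 in P and O (opposite signs); a within-person P-O correlation r; a random-slope variance τ².

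**Step 1: the plan's own figure.** Person-mean centring leaves 65 × (7 − 1) = 390 within-person degrees of freedom. For one standardized predictor, SE² = 1/390 + τ²/65.
- With fixed slopes (τ² = 0), SE = 0.0506, b/SE = 3.55 and power = Φ(3.55 − 1.96) = 0.945. A simulation of 4,000 data sets gave 0.94.
- With τ² = 0.10, SE = √(0.002564 + 0.001538) = 0.0640, b/SE = 2.81 and power = 0.80.

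The 0.8 thus follows in this approximation only with a slope variance that the document does not state. It comes from an outside guide and cannot be confirmed or refuted here. The next two steps take it as given.

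**Step 2: both coefficients at 0.8.** Independent estimates give 0.8 × 0.8 = 0.64. Whatever the dependence, the joint probability is at least 0.8 + 0.8 − 1 = 0.60 and at most 0.80.

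**Step 3: P-O correlation.** A power of 0.8 corresponds to a noncentrality of 1.96 + 0.84 = 2.80. With positive r, the O statistic and the sign-reversed P statistic correlate at r. Joint power is the bivariate normal probability that both exceed 1.96. There are two readings of the 0.8:
- (a) it already reflects collinearity, so the noncentrality stays at 2.80;
- (b) it does not, so the noncentrality becomes 2.80 × √(1 − r²).

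| r (assumed) | Joint power, reading (a) | Each coefficient, reading (b) | Joint power, reading (b) |
|---|---|---|---|
| 0 | 0.64 | 0.80 | 0.64 |
| 0.3 | 0.67 | 0.76 | 0.61 |
| 0.5 | 0.69 | 0.68 | 0.53 |
| 0.7 | 0.71 | 0.52 | 0.39 |

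On the same anchor, the effect with 0.8 joint power is about 0.21 at r = 0 (0.18 × 3.21/2.80). At r = 0.7 it is about 0.20 under (a) and 0.28 under (b).

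**Step 4: without the 0.8 as anchor.** Here the variance of each coefficient is 1/[65(m − 1)(1 − r²)] + τ²/65. Joint power at 0.18 for r = 0 / 0.5 / 0.7:

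| τ² (assumed) | 7 intervals | 5 intervals |
|---|---|---|
| 0 | 0.89 / 0.79 / 0.61 | 0.68 / 0.57 / 0.42 |
| 0.05 | 0.77 / 0.67 / 0.52 | 0.57 / 0.49 / 0.37 |
| 0.09 | 0.67 / 0.59 / 0.46 | 0.49 / 0.43 / 0.33 |

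Simulation with 7 intervals gave 0.90 / 0.78 / 0.63 at τ² = 0 and 0.57 / 0.49 / 0.39 at τ² = 0.09.

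**Step 5: usable intervals.** An interval with no recorded exposure has no mean P or mean O. Guided exposures end at session 9, so the intervals from 10 to 11 and from 11 to 12 rest on homework alone. Seven per person is therefore the most that can be obtained. Five is an illustration, not a forecast.

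**Step 6: fallback.** The analysis below 50 participants is condition-based regression, which the Introduction says also needs both coefficients significant. At 0.8 each, joint power is again 0.64 if independent. No numerical value is given for its medium effect, so nothing more can be computed.

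**The case against.** The strongest reply is that the size of the shortfall depends on quantities the document does not contain. That stands. A reader might infer that the design's real power is about 0.4 to 0.65, but the documents do not support this. The lower end needs a P-O correlation near 0.7 and the reading that 0.8 ignores collinearity. Parallel items on a common scale make some correlation plausible, but do not establish its size for interval means. With fixed slopes and 7 intervals, joint power is 0.79 or more up to r = 0.5. That case is not a defence of the printed figure, however: it implies 0.945 for one coefficient and so replaces the stated 0.8.

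A reader might also infer that late intervals rest on voluntary homework, or that an omitted dropout allowance is itself an error. Neither follows. Homework exposures are assigned by therapists, surveys are reimbursed, missing data are expected and their handling is named, and an article may leave an allowance to the full protocol. Missing intervals matter here only because they push power further down.

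Finally, the primary aim is worded as exploratory, and no estimate or test would change. This limits the consequences, but the section still offers its figure as adequate for the primary analyses, and the success rule is explicit.

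**Conclusion.** The mismatch holds and can be read from the text: a power figure for a level-one effect is offered for a hypothesis that needs two significant coefficients. With 0.8 for each, power for the rule is 0.64 under independence and stays below 0.8 for any P-O correlation short of 1. It is about 0.60 to 0.71 if the 0.8 already includes collinearity (0.60 is the general lower bound, 0.71 the value at r = 0.7). If it does not, power is about 0.61, 0.53 and 0.39 at assumed correlations of 0.3, 0.5 and 0.7. All these values assume a true effect of 0.18 in both coefficients. A larger effect in one would raise joint power, but not above the 0.8 of the other. The model-fit condition and empty intervals would lower it. The document does not show that the 0.8 was miscalculated for one coefficient, or that 65 participants are too few to proceed.

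**What to change.** Restate the power in the Sample size section for the rule actually used: both coefficients significant with the predicted signs. Give either the joint power at 0.18 or the effect detectable with 0.8 joint power. Obtain it from a short simulation of the planned model over stated ranges of P-O correlation (for example 0.3 to 0.7), random-slope variance (including zero) and usable intervals per person (for example 5 to 7). Say whether the 0.18 is a partial coefficient in the fitted model. Do the same for the 30 × 5 fallback, with a number for its medium effect.

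The cost is one paragraph and a small simulation. Recruitment, conduct and the analysis model are unchanged. The drawback is a less favourable stated figure.

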The secondary aim of the study is whether the average prediction error experienced during treatment predicts treatment outcome. We hypothesize that participants who experienced greater symptom improvements from baseline to 3-month follow-up will have experienced greater overall threat prediction error in their exposures during treatment. For each participant, we will calculate their mean P and O experienced across all exposures in treatment (termed txP and txO, respectively). The outcome will be symptoms at 16 time points from baseline to 3-month follow-up. We will examine the interaction of assessment point with txP and the interaction of assessment point with txO on the outcome. The hypothesis would be supported if both interactions were significant, and txO is positive in sign and txP is negative in sign. The secondary hypotheses will be exploratory because cross-level interactions likely require larger sample sizes to be adequately powered to detect a medium effect size (92).

The tertiary aim of the study is to explore whether prediction error relates to surprise and learning outcomes. We hypothesize that the larger prediction error (regardless of type) will predict larger feelings of surprise after an exposure and greater likelihood for participants to report a learning outcome. We will use the EMA data without aggregation to perform multi-level RSA with surprise as the outcome and P and O and their higher order terms as predictors. Response surface parameters will be examined to determine whether the hypothesis is supported (49, 50, 53).

We will test whether session modality (in-person vs. video teleconference) affects outcomes by adding it as a level one predictor to all final models. We retain it as a control variable if it improves model fit. We will check the internal consistency of the threat prediction and outcome measures (other exposure measures are single item) using multilevel modeling [see (93)]. We will check the validity of exposure process measures by looking for expected patterns of associations among these variables (94).

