### Progress

Recruitment began in 2019 and will aim to end by 2023. Thirty-one people have participated in the study as of January 2022. The original study protocol developed in 2019 and went through modifications due to the COVID-19 pandemic, technical issues, and unavoidable changes to clinic procedures. These changes are described below.

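### Below 50 participants the plan drops the test of non-linear discrepancy because REML likelihoods cannot be compared, but that does not make the test unavailable

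*Protocol article*

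**What the plan says.** The Analysis section sets two coefficient conditions for the primary hypothesis: mean threat outcome (O) significant and positive, mean threat prediction (P) significant and negative. It then adds a second-order model with P², P×O and O², and makes support depend on the linear model being preferred to it. Fit is to be compared by likelihood-ratio tests under maximum likelihood (ML).

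The Sample size section gives a contingency: "If the actual sample size is low (less than 50), we will use restricted maximum likelihood estimation with small sample corrections". In that case the primary analysis keeps only the linear discrepancy model, with condition-based regression analysis (CRA), and "We would not be able to test whether complex or non-linear discrepancy models fit the data better than linear discrepancy effects". The reason stated is that REML does not "permit meaningful comparison of models that differ in fixed effects". Low power and overfitting are not mentioned.

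Two other places bear on this. The Analysis section adds session modality to all final models and says: "We retain it as a control variable if it improves model fit". The Progress section reports: "Thirty-one people have participated in the study as of January 2022", with recruitment from 2019 and an aim to finish by 2023.

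**The concern.** The premise is right and the conclusion is not. A restricted likelihood depends on the fixed-effect design, so two REML fits with different fixed effects cannot be put into a likelihood-ratio test. But whether three coefficients are all zero is a question about one model, and it needs no comparison of likelihoods. The plan already intends small-sample corrections with REML, and these are what a valid joint test of coefficients requires.

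At stake is part of the answer to the primary aim. The Introduction presents the analytic treatment of complex mismatch effects as something earlier therapy studies lacked. Below 50 participants the plan would give that up for symptom change, and with it one condition of the support rule. The primary hypothesis would then be judged on fewer conditions at 49 participants than at 50, for a reason that does not require it.

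**Working it through.** **1. The plan's own figure.** The Sample size section states 65 participants, 7 observations each, a standardized effect of 0.18, and detection "with 0.8 power at a significance level of 0.05 and assuming a large intraclass coefficient of 0.5". A normal approximation for a within-person effect is SE = √[(1/(n−1) + τ²)/N], with power = Φ(0.18/SE − 1.96), two-sided. The random-slope variance τ² is not stated, so it is varied here.
- τ² = 0: SE = √(0.1667/65) = 0.0506; power = Φ(3.555 − 1.96) = 0.945.
- τ² = 0.10: SE = √(0.2667/65) = 0.0640; power = Φ(2.810 − 1.96) = 0.802.

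The stated 0.80 is matched at an assumed τ² of about 0.09 to 0.10. It is plausible but not fixed by the stated inputs, and the point does not rest on it.

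**2. Why REML likelihoods cannot be compared.** The restricted log-likelihood contains −½ log|X′V⁻¹X|. Multiplying the three second-order columns by 0.01 leaves the model unchanged, but shifts twice the log-likelihood by 3 × 2 × ln(100) = 27.6. The 5% critical value on 3 df is 7.81. In simulation with 40 participants, this naive test rejected a true null in 0% of runs on the original scale and 100% after that rescaling. The protocol is right to reject it.

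**3. Whether a valid test exists below 50.** The simulated model has a random intercept with intraclass correlation 0.5, 7 occasions, person-mean-centred P and O, their person means and two controls. The true effects are linear (−0.18 and +0.18) with no curvature. There were 2,000 runs per N, so the Monte Carlo SE is √(0.05 × 0.95/2000) = 0.0049. The REML test is F = b′V_b⁻¹b/3 on the three coefficients, with denominator df N(7−1) − 7 (for example 40 × 6 − 7 = 233).

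| N | REML joint F, 3 df | ML refit, likelihood ratio, 3 df | Modality, REML t |
|---|---|---|---|
| 15 | 0.0540 | 0.0690 | 0.0550 |
| 31 | 0.0530 | 0.0625 | 0.0465 |
| 40 | 0.0515 | 0.0560 | 0.0495 |
| 49 | 0.0565 | 0.0585 | 0.0430 |
| 65 | 0.0560 | 0.0585 | 0.0530 |

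The REML F test is at most (0.0565 − 0.05)/0.0049 = 1.3 Monte Carlo SEs above nominal. The ML refit is slightly liberal at small N: 3.9 SEs above at 15 and 2.6 at 31.

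**4. Power of that test.** For an assumed, illustrative curvature of 0.08 on (P − O)², with 1,000 runs per N, the REML F test rejected in 0.155 (N = 31), 0.192 (40), 0.215 (49) and 0.258 (65).

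**5. How live the fallback is.** January 2022 is taken as 2022.04. The start month in 2019 is not given, so January and mid-year are both tried.
- Rate: 31/(2022.04 − 2019.0) = 10.2 a year; 31/(2022.04 − 2019.5) = 12.2 a year.
- Start of 2023: 31 + 0.96 × 10.2 = 40.8; 31 + 0.96 × 12.2 = 42.7.
- End of 2023: 31 + 1.96 × 10.2 = 51.0; 31 + 1.96 × 12.2 = 54.9.
- Needed for 65 by the end of 2023: (65 − 31)/1.96 = 17.3 a year.

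**The case against.** The strongest defence is that the plan fixed likelihood-ratio tests as its way of comparing fit, and within that choice its statement about REML is correct. It also avoids ML at small N with some cause, since the ML refit is mildly liberal there. Both points stand. They show that the reason is incomplete, but not that the test is unavailable.

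Low power is a second defence. On the illustrative curvature, power at 31 to 49 participants is about 0.16 to 0.22, so restoring the test may rarely change the conclusion. That also stands, but the protocol does not give it as the reason. At 65, where the plan does run the test, power is only about 0.26, so power does not explain a cut at 50.

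A reader might infer more than the document supports:
- *That the fallback disables the modality step.* The Analysis section names no likelihood-ratio test for modality, and the Sample size section limits the consequence to the primary analysis. A single coefficient can be tested under REML. At most, the fit criterion in that case is unstated.
- *That the fallback contradicts the support rule.* It openly substitutes a reduced analysis, and the two CRA coefficient conditions work under REML. A declared contingency that drops one condition is not a contradiction.
- *That fewer than 50 is the probable outcome.* The end-of-2023 projection exceeds 50. Falling below it needs an earlier end date or losses that the document does not quantify, and the rate comes from a period that includes lockdowns and suspended in-person treatment.
- *That ML at 65, or the switch at 50, is an error.* At 65 the ML test rejected 0.0585 and the REML F 0.0560, which gives no ground for changing the main estimator.

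**Conclusion.** The point holds in limited form. The statement that non-linear discrepancy could not be tested below 50 is wrong as written: the stated property of REML likelihoods is correct, but a joint test of the three coefficients within one REML fit is available and held its level at 0.0515 to 0.0565 for 15 to 65 participants. The consequence is the avoidable loss, below 50, of one condition of the support rule. The linear hypothesis itself remains testable.

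The simulation rests on random intercepts only, complete data in all seven intervals, assumed predictor distributions, and no lagged symptom term. Its denominator df stood in for a Kenward-Roger or Satterthwaite calculation. With random slopes the df would fall towards the number of participants, which still suffices for a 3-df test. The validity of a joint coefficient test under REML is general; the exact rejection rates are not. The recruitment projection assumes a constant rate and counts people enrolled, not people analysed.

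**What to change.** Keep the REML fallback below 50 and replace the sentence on non-linear models with wording such as:

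> The three second-order terms (P², P×O, O²) will be tested jointly within the REML fit by a small-sample-corrected F test (Kenward-Roger or Satterthwaite), and the support rule in the Analysis section will be applied using that test.

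An ML refit used only for the comparison is an alternative, with its slight liberality at small N acknowledged. Add that the same kind of coefficient test decides whether modality is kept when REML is used. Add also that, given low power, a non-significant joint test means the linear model was not rejected and is not evidence of linearity.

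The cost is a few sentences. No new data are needed, the corrections are of the kind the plan already adopts, and neither the estimator at 65 nor the switch at 50 need change.
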